### Interventions

#### ECT group (control group)

##### Anesthesia

Patients will be administered etomidate for anesthesia, succinylcholine as a muscle relaxant, and atropine for the suppression of gland secretions, and pure oxygen will be supplied during each treatment session.

##### Placement of stimulation electrodes

Because bitemporal electrode placement achieved a more rapid and earlier decrease in symptom ratings [13], bitemporal electrode placement will be used on each patient. For the bitemporal electrode placement, the two electrodes are applied 2–3 cm above the midpoint of the line connecting the outer canthus of the eye and the external auditory meatus on each side of the head [13].

##### Stimulus and seizure threshold (ST) titration

The ECT or LCE procedure will be administered with a spECTrum 5000Q ECT instrument (MECTA Corporation, OR, USA) three times a week. The pulse width is set to 1 ms, and the current is set to 800 mA. The ST titration procedure basically follows Mankad et al. [12]. The energy set of the first ECT session uses the titration procedure described in the Additional file 1: Table S1. If the seizure induction is unsuccessful or the seizure lasts less than 15 s (based on electroencephalogram (EEG)), the patient will be restimulated at a higher energy level after a short delay. The restimulation process could be repeated up to three times during the first treatment. If all four stimulations fail to induce an adequate seizure, the dose set for the titration in the next session will be set at 2 steps higher than the last stimulation dose. The ECT charge dose for subsequent treatments is set as follows: 1.5 * ST, similar to Kellner et al. [13].

##### Seizure adequacy

Seizure detection is performed using a single channel EEG from the ECT instrument. The seizure duration recorded by EEG is checked by a certified electroencephalographer who is blinded to the participant’s status.

#### Hybrid-ECT group (treatment group)

##### Anesthesia

Same as the ECT group.

##### Placement of stimulation electrodes

Same as the ECT group.

##### Stimulus

The energy set of the first three sessions is the same as that in the ECT group; the subsequent sessions use LCE, and the energy is set to the minimum (2.8 J) with a stimulus duration = 0.5 s and a frequency = 20 Hz, as we have previously reported [22].

##### Seizure adequacy

Same as the ECT group.

##### Follow-up scheme

To evaluate the acute and chronic influence of ECT and Hybrid-ECT respectively, we set a two-stage follow-up schedule (see Table 1). The first follow-up phase is set at the one-month after the last ECT/LCE session, and the second phase is a one-year follow-up following the first phase (see Table 1).

**Table 1 Tab1:**
[figure not shown]
Visit procedure

a: test after every ECT/LCE session

HAMD-24: Hamilton depression rating scale, *HAMA* Hamilton anxiety rating scale, *CGI* Clinical global impressions, *YMRS* Young mania rating scale, *PANSS* Positive and negative syndrome scale, *SF-36* MOS 36-item short-form health survey, *SDS* Self-rating depression scale, *SAS* Self-rating anxiety scale, *EMQ* Everyday memory questionnaire, *WAIS* Wechsler adult intelligence scale 4th edition, *MMSE* Mini-mental state examination, *RBANS* Repeatable battery for the assessment of neuropsychological status, *ORT* Orientation recovery test

##### Randomization

After receiving detailed information about this trial, signing the consent form, passing the eligibility screen and completing the baseline test, the enrolled patients will be assigned a sequential patient number. If a patient discontinues from the study between the randomization and the first ECT procedure, the patient will be excluded from the final analyses, and he or she will not be allowed to rejoin the study.

A statistician with no other connection to the trial will generate the randomization sequence using the default random number generator of SAS version 9.4 (SAS Institute Inc., Cary, NC, USA). The randomization sequence list will remain concealed from the investigators. A research nurse who will not participate in the clinical evaluation will assign the participants to their group.

Participants, neuropsychological measurement raters, MRI and ERP operators, patient psychiatrists, nurses, and researchers will be blinded to the patient treatment assignment. If unblinding is determined to be necessary, the investigators must report all unblinding (with reason) on the corresponding case report form (CRF).

##### Assessment of the effectiveness of the blind methods

Participants and raters will be asked to which group the participant had been allocated, and about the strength of confidence of their guess as well as the reasons for their guess at every visit after the randomization. The ratios of right guesses/wrong guesses will be used to assess the effectiveness of the blinding procedure.

##### Medication during ECT/hybrid-ECT sessions

Patients in both arms will be maintained on their previously prescribed antidepressants and antipsychotics (usually used for patients with bipolar depression and patients with depression and psychotic symptoms) during the trial. Anticonvulsant drugs, lithium, or mood stabilizers will be discontinued during the course of ECT/Hybrid-ECT treatment. Patients exhibiting agitation or feeling anxious could be temporarily administered short half-life benzodiazepines, but the administration of benzodiazepines will be prohibited 24 h before the ECT/LCE session. When patients suffer from insomnia, zopiclone, eszopiclone, or zolpidem can be temporarily given to help them sleep.

##### Medication during the follow-up phase

Medication during the follow-up period is essentially the same as that during the ECT/Hybrid-ECT phase; however, lithium, mood stabilizers, or antiepileptic drugs are allowed. The detailed and individualized pharmacological plan will be determined by the patient’s psychiatrist.

### Outcome measures

#### Visit procedure

Patients will be interviewed during twelve visits. The detailed visit procedure is shown in Table 1.

#### Primary outcome measure

The primary outcome measure is the change in total HAMD-24 score at endpoint (visit t_5_) from baseline.

#### Secondary outcome measures

The secondary outcome measures include the response rate (defined as a HAMD-24 score that shows a more than 50% reduction from the baseline) and remission rate (remission is defined as HAMD-24 score < 10) at t_5_ and the scores on the Clinical Global Impressions (CGI) scale [26], Positive and Negative Syndrome Scale (PANSS) [27], MOS 36-item Short-form Health Survey (SF-36) [28], Hamilton Anxiety Rating Scale (HAMA) [29], YMRS [25], Self-Rating Depression Scale (SDS) [30], Self-Rating Anxiety Scale (SAS) [31], and Everyday Memory Questionnaire (EMQ) [32].

#### Neuropsychological assessment

A comprehensive neurocognitive battery will be performed, as presented in Table 1. Neuropsychological evaluations will be carried out by trained psychologists who will be blinded to the patient groups. The cognitive domains to be tested include general intelligence, global status, attention, processing speed, language, visuospatial function, executive function and memory. IQ will be assessed by the Wechsler Adult Intelligence Scale 4th edition [24]. A modified version of the Mini-Mental State Examination (MMSE) [33] will be used to test global status. The Repeatable Battery for the Assessment of Neuropsychological Status (RBANS) is designed to assess attention, language, visuospatial, immediate memory and delayed memory [34]. Processing speed will be assessed by the digit symbol test [35]. Stroop reaction time, Stroop color-word test [36] and trail making test (A, B) [37] will be used for examination of executive function. Orientation recovery is assessed at every ECT/LCE session. The time to orientation test is assessed with continuous questioning on five items (name, place, day, age, date of birth) for 90 min [38]. A correct response on four of five items is required. Patients who do not meet the criteria for recovery are assigned scores of 100 min. The subjective cognitive evaluation will be evaluated by the Squire Subjective Memory Questionnaire [39].

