### Statistical analyses

#### Neuropsychological and clinical outcomes

Demographic and baseline data will be analyzed using independent two-sample *t*-tests or chi-square tests (or Fisher’s exact tests). All analyses of clinical outcomes, neuropsychological results and safety indicators will be performed for the modified intent-to-treat population (MITTP) (at least one treatment and at least one postbaseline measure). We will use mixed-effects model repeated measures (MMRM) as the main analysis for the comparison of the primary and continuous secondary outcome measures. We will use chi-square/Fisher’s exact tests to analyze the categorical outcome measures. We will use a “tipping point” analysis to assess the robustness of the primary analysis (MMRM) to possible deviations from the missing at random (MAR) assumption. The significance level will be set to 0.05 (two tailed). All statistical analyses will be performed with SAS (ver. 9.4) software (SAS Institute Inc., Cary, NC, USA). MRI and ERP data analyses will be performed by using the relevant professional software packages (FreeSurfer [54], FSL [55], EEGLAB [56], etc.*)*.

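### Scoring an unrecovered session as 100 min replaces a time censored at 90 min with an arbitrary constant, so any mean difference in reorientation time depends on that constant

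*Protocol article*

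**What the plan says.** Under Neuropsychological assessment, the protocol article sets out the measure in four steps:

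- Reorientation is measured each time a patient is treated, with either type of stimulus.
- The test consists of "continuous questioning on five items (name, place, day, age, date of birth) for 90 min".
- A patient counts as reoriented once four of these five answers are right.
- For everyone else the scoring rule reads: "Patients who do not meet the criteria for recovery are assigned scores of 100 min".

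Under Statistical analyses (Neuropsychological and clinical outcomes), it names "mixed-effects model repeated measures (MMRM) as the main analysis for the comparison of the primary and continuous secondary outcome measures". For the rest: "We will use chi-square/Fisher’s exact tests to analyze the categorical outcome measures". Neuropsychological results are to be analysed in the modified intent-to-treat population. No time-to-event or rank-based method is named, and no test is named for reorientation time in particular. The measure does not appear under Secondary outcome measures. The article gives no expected recovery times and no expected share of patients unrecovered at 90 min.

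**The concern.** A patient still disoriented when questioning ends has a right-censored time. The rule turns this into an exact value that nobody observed. In a mean, or in a model for means, that value counts as a measurement.

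The second hypothesis in the Background is that Hybrid-ECT causes fewer adverse effects, mainly after the third session. Reorientation is measured at every session, so it can separate the first three sessions, which use the same energy setting in both arms, from the later ones, where treatment differs. If the hypothesis is right, unrecovered sessions may be more frequent with ECT from session 4 onward. The constant would then not cancel between arms. At stake is the size of a reported cognitive side-effect difference, not the primary efficacy conclusion.

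**Working it through.** **1. The plan's own figure.** The only derived figure is the sample size for HAMD-24 change (margin 4.0, SD 8.0, one-sided alpha 0.05, power 0.8, drop-out 10%). Per arm, n = 2 × (1.645 + 0.842)² × (8/4)² = 49.5, rounded up to 50. Then 50/0.9 = 55.6, rounded up to 56, and 2 × 56 = 112. It reproduces and does not involve reorientation time.

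**2. Dependence on the constant.** Let pE and pH be the shares unrecovered at 90 min with ECT and Hybrid-ECT. Raising the assigned score by one minute changes the mean difference (ECT minus Hybrid) by pE − pH minutes, whatever the distribution. With pE = 10% and pH = 0 (assumed), scoring 120 instead of 90 moves the result by 30 × 0.10 = 3 min on identical data.

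**3. Direction of the error.** Let mE and mH be the mean true times of the unrecovered. The error in the mean difference is pE(100 − mE) − pH(100 − mH). If both arms share the same m, this is (pE − pH)(100 − m). With pE = 10% and pH = 0:

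| m (min, assumed) | Error (min) |
|---|---|
| 92 | +0.8 (overstated) |
| 95 | +0.5 |
| 100 | 0 |
| 105 | −0.5 |
| 120 | −2.0 |
| 150 | −5.0 (understated) |

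With pE = pH and the same m, the error is zero. With pE = 2% and pH = 0, it runs from +0.16 (m = 92) to −1.0 min (m = 150).

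**4. Size under assumed lognormal times.** All medians and log-SDs are assumptions.

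| Medians ECT/Hybrid (min) | Log-SD | Unrecovered ECT/Hybrid | True difference (min) | With 100 assigned (min) | Ratio |
|---|---|---|---|---|---|
| 20/10 | 0.5 | 0.1% / 0.0% | 11.33 | 11.33 | 0.999 |
| 45/15 | 0.3 | 1.0% / 0.0% | 31.38 | 31.38 | 1.000 |
| 45/15 | 0.5 | 8.3% / 0.0% | 33.99 | 32.71 | 0.962 |
| 30/10 | 0.8 | 8.5% / 0.3% | 27.54 | 24.38 | 0.885 |
| 45/30 | 0.8 | 19.3% / 8.5% | 20.66 | 13.84 | 0.670 |
| 60/20 | 1.0 | 34.3% / 6.6% | 65.95 | 32.09 | 0.487 |
| 80/60 | 1.0 | 45.3% / 34.3% | 32.97 | 8.65 | 0.262 |

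Check of the 45/30 row by step 3, with mE = 151.9 and mH = 137.9: 0.1931 × (−51.9) − 0.0848 × (−37.9) = −10.02 + 3.21 = −6.81. The table gives 13.84 − 20.66 = −6.82, which agrees within rounding. By step 2, the same case scored 90 or 120 gives 13.84 − 10 × 0.1083 = 12.76 or 13.84 + 20 × 0.1083 = 16.01 min.

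**5. Power.** Simulated with 50 per arm, one session, two-sided 5%, medians 45/30, log-SD 0.8, 2,000 runs: t-test on the full true times 0.58, t-test with 100 assigned 0.66, Wilcoxon 0.68, log-rank censored at 90 min 0.64. A separate set of 600 runs per case, log-SD 0.8, with 100 kept except in the censored model:

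| Medians | t-test, minutes | t-test, log | Wilcoxon | Censored lognormal |
|---|---|---|---|---|
| 30/20 | 0.66 | 0.73 | 0.72 | 0.74 |
| 45/30 | 0.63 | 0.69 | 0.66 | 0.70 |
| 60/40 | 0.68 | 0.69 | 0.69 | 0.70 |

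Taking logs with the score kept comes within about 0.01 of the censored model, which is also the model that generated the data.

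**The case against.** The strongest reply is that the article fixes a scoring convention, not an analysis. Reorientation time is outside the secondary outcome list, no test is assigned to it, and a statistical analysis plan that is not shown may treat it properly. The convention also rules nothing out. Since 100 lies above every observable time, rank tests are unaffected, and every 100 can be recoded as censored at 90 without loss.

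Most of this stands, and it is why the use of MMRM here is called an inference. It does not remove the point. The rule itself is stated, it produces a number of minutes, and the only repeated-measures method named is one for means.

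Two stronger readings are tempting, and the documents support neither:

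- **That the rule understates the difference between arms.** This needs more unrecovered sessions with ECT and a mean true time above 100 min among them. The article gives neither quantity, so even the direction is open.
- **That the rule costs power.** In the simulations, scoring 100 did not lower power relative to a t-test on the full times. Most of the gap to the censored model comes from analysing skewed minutes untransformed.

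It is also fair to say that the mean beyond 90 min cannot be observed under any method. The true differences in the table rest on the assumed tail.

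**Conclusion.** The point holds in a limited form. The 100-min score is an arbitrary substitute for a time known only to exceed 90 min, and any mean difference depends on it.

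- The difference can be understated if ECT has more unrecovered sessions and their mean true time exceeds 100 min.
- It is slightly overstated if that mean lies between 90 and 100 min.
- It is essentially unaffected if few sessions are unrecovered, or if the unrecovered share and their mean true time are equal in both arms.

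Under assumed lognormal times the effect runs from nil to about half the true difference when up to about a third of ECT sessions are unrecovered. It exceeds half only in more extreme cases, such as 80/60 with log-SD 1.0. The article does not say where this trial would fall. The conclusion assumes that means are compared, which the article implies but does not state for this measure. The primary outcome and N = 112 are untouched. Label: cheap improvement.

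**What to change.** State, before unblinding, that a session without recovery is right-censored at 90 min. Analyse reorientation time with a time-to-event or censored log-time model that allows for repeated sessions per patient, or with a rank-based test. Focus the comparison on session 4 onward, where the arms differ. Report the proportion unrecovered at 90 min by arm, and keep the 100-min score as a descriptive summary only.

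The cost is a change of analysis wording and of statistical procedure. No new data are needed. The downside is that a time ratio, hazard ratio or rank comparison is less familiar to readers than mean minutes, and a censored log-time model brings its own distributional assumption.

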#### MRI and ERP acquisition

ECT can cause changes in brain function [40], metabolism [41], and structure [42], especially in hippocampal volume [43], which may be related to neurogenesis in the hippocampal dentate gyrus, so the aims of our MRI and ERP are as following: 1) use the MRI to observe the changes of hippocampus in volume before and after treatment and between the two groups; 2) use the fMRI and DTI to observe ECT/LCE-related activation, functional connections, and changes in nerve fiber connections; 3) use MRS to observe metabolic changes of hippocampus before and after ECT; 4) use ERP to observe the EEG changes related to ECT/LCE.

#### MRI protocol

MRI will be performed at 3 time points: t_0_ (~ 24–48 h before baseline), t_1_ (~ 24–48 h after the three first ECT and before the fourth ECT/LCE) and t_5_ (~ 7 days the last of ECT/LCE). All participants will be scanned at the Shenzhen Kangning Hospital Neuropsychiatry Imaging Center in a 3 T Discovery MR750 scanner (GE Healthcare, Milwaukee, USA) equipped with an eight-channel head coil. A standard MRI protocol will be applied at each time point, including a T1-weighted spoiled gradient echo, SPGR (TE = min full; TR = 6.7 ms; flip angle = 12°; field of view =256 mm; voxel size = 1.0 * 1.0 * 1.0 mm^3^; matrix = 256 * 256); a T2-weighted high resolution hippocampus sequence (TE = 50 ms; TR = 8020.0 ms; flip angle = 122°; field of view =175 mm; voxel size = 0.4 * 0.4 * 2.0 mm^3^; matrix = 448 * 448); a resting-state fMRI scan with a BOLD sequence (TE = 25 ms; TR = 2000 ms; field of view =220 mm; voxel size = 3.4 * 3.4 * 3.2 mm^3^; matrix = 64 * 64; volume number = 240); a DTI sequence (TE = 81.4 ms; TR = 8724.0 ms; field of view = 224 mm; voxel size = 2.0 * 2.0 * 2.0 mm^3^; matrix = 112 * 112; number of diffusion directions = 64; b values = 0, 1000 s/mm^2^); ^1^H- magnetic resonance spectroscopy (MRS) sequences for the ROIs including the hippocampus, thalamus, anterior cingulate and posterior cingulate (TE = 35.0 ms; TR = 1500 ms) [44–46]; and a 3D ASL sequence (TE = 10.5 ms; TR = 4389 ms; post-labeling delay = 1025 ms; field of view =240 mm).

#### ERP measures

The ERP data will be recorded using BrainAmp Amplifier (Brain Products GmbH, [name]), and electrodes will be placed at 32 scalp locations based on the 10–20 system [47]. An electrode linked ears/mastoid reference scheme will be used. The electrode impedance will be kept below 10 KΩ. Amplifiers will have a bandpass of 0.1–50 Hz, and the stimulus rate will be 0.5 Hz. Continuous EEG records, at a sampling rate of 1000 Hz, will be stored for further off-line analysis. In the ERP experiment, the patients will be told to stay relaxed and quiet. P300 and P50 paradigms and 3-min resting-state EEG recording with eyes closed will be selected for the measurement index of cognitive function. The classic auditory oddball paradigm will be used to measure P300. The classic P300 task will include a total of 200 target and standard stimuli, and the 40 target stimuli will be a tone at 60 dB of low frequency (20%) and high pitch (2000 Hz), and the 160 standard stimuli will be a tone at 80 dB of high frequency (80%) and low pitch (1000 Hz). The two stimuli presentations last 20 ms. The participant will need to click a button as soon as they hear the stimuli to judge whether a tone was a standard stimulus or target stimulus [48, 49]. P50 will be examined using conditioning (S1)-testing (S2) paired acoustic stimulation with short wavelength and sound pressure set at 105 dB. The first click produces an excitatory response and activates inhibitory pathways, and the response to the second click is normally suppressed. The pairs of clicks will be presented 500 ms apart and the interval between two paired stimuli is 10 s [50, 51]. P50 is measured by the P50 ratio, which will be calculated as the S2 amplitude divided by the S1 amplitude. A P50 ratio closer to 0 is indicative of robust suppression (gating), whereas a ratio closer to 1 is indicative of diminished sensory gating [52]. The ERP procedures will be performed according to the MRI schedule.

#### Safety assessment and AEs

Safety data will include clinical examinations, blood tests, electrocardiogram (ECG), urine tests, and cognitive function assessments.

#### AEs

Any untoward medical occurrence during ECT/Hybrid-ECT treatment, which may or may not be causally linked with the ECT/LCE treatment, will be defined as an AE. All AEs will be recorded in the CRF. An important focus of this trial is to explore whether there are fewer side effects from Hybrid-ECT than from routine ECT, in addition to comparing total AE numbers and severity; therefore, all AEs will be categorized according to when they occurred (initial three ECT sessions or the subsequent ECT/LCE sessions) for further analyses.

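### The adverse-event definition and both its analysis periods stop at the last session, so no discrete event in the 13-month follow-up enters the AE comparison

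*Protocol article*

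**What the plan says.** The AEs section of the protocol article defines the event: "Any untoward medical occurrence during ECT/Hybrid-ECT treatment, which may or may not be causally linked with the ECT/LCE treatment, will be defined as an AE". It names comparison of total AE numbers and severity as a focus of the trial, and adds that "all AEs will be categorized according to when they occurred (initial three ECT sessions or the subsequent ECT/LCE sessions) for further analyses". These are the only two periods given.

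The Follow-up scheme section gives the purpose of later observation: "To evaluate the acute and chronic influence of ECT and Hybrid-ECT respectively, we set a two-stage follow-up schedule". On its length it says: "The first follow-up phase is set at the one-month after the last ECT/LCE session, and the second phase is a one-year follow-up".

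The section on medication during follow-up treats the two phases as distinct: "Medication during the follow-up period is essentially the same as that during the ECT/Hybrid-ECT phase".

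The Safety assessment section lists other safety information without an end date: "Safety data will include clinical examinations, blood tests, electrocardiogram (ECG), urine tests, and cognitive function assessments".

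The second hypothesis, in the Background, is that Hybrid-ECT may cause fewer AEs, with emphasis on the part of treatment after the third session.

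**The concern.** The definition and the two periods agree with each other, so the restriction is not one loose word. A later analysis plan would inherit a rule under which a post-course event is not an AE and need not be entered as one on the case report form. What was not recorded cannot be recovered at analysis.

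The arms differ in what is given from the fourth session to the last. If that difference affects how long the benefit lasts or what follows it, the resulting discrete events would tend to come after the last session. The Background itself stresses suicide risk in this population. The Perspectives section looks ahead to a general statement that Hybrid-ECT has fewer side effects. An AE comparison that closes with the last session cannot support that statement for the period afterwards, although the trial keeps patients under observation for it.

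**Working it through.** The plan attaches no figure to the AE comparison. Its one computed design figure, the sample size, reproduces and does not bear on this point: 2 × (1.645 + 0.842)² × 8² / 4² = 49.5, so 50 per arm; 50 / 0.9 = 55.6, so 56 per arm and 112 in total. Changing the AE window alters neither this number nor the significance level. The check is therefore a comparison of sections.

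1. **Does treatment, in the AE definition, include follow-up?** The two medication sections give separate rules for the ECT/Hybrid-ECT course and for the follow-up period. The follow-up is counted from the last session. Treatment therefore means the course of sessions.

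2. **Do the analysis periods reach further than the definition?** No. One covers sessions 1 to 3 and the other the later sessions. An event after the last session fits neither.

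3. **How much planned observation lies outside?** One month plus one year: 1 + 12 = 13 months. On the literal wording this is all of the follow-up.

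4. **Where does the primary endpoint fall?** The primary outcome is read at t5. The MRI protocol section places the t5 scan at "t_5_ (~ 7 days the last of ECT/LCE"; a word is missing, and I read it as about 7 days after the last session. If the t5 visit coincides with the scan, the AE window closes about a week before the primary endpoint.

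5. **Share of observed time.** The number of sessions is not given in the text. Assume 6 to 12 sessions at the stated three per week, that is 2 to 4 weeks, with follow-up of 4.3 + 52.1 = 56.4 weeks. Share = course / (course + 56.4):
   - 2 weeks: 2 / 58.4 = 3.4%
   - 3 weeks: 3 / 59.4 = 5.1%
   - 4 weeks: 4 / 60.4 = 6.6%

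   This is a share of calendar time under an assumed course length. It is not a share of events.

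6. **What else could capture a late harm?** The Safety assessment list has no end-of-treatment limit, and the outcome sections name scales for mania, memory complaints and cognition. Table 1, which schedules them, is not reproduced in the text available, so which of them continue into follow-up cannot be checked. Whatever the schedule, these are measurements at visits. They do not count a suicide attempt or a readmission as an event, and they do not reach a patient who misses the visit.

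**The case against.** The strongest reply is that the window suits the question. The second hypothesis stresses the later part of treatment, the Background names headache, dizziness and confusion as typical adverse effects, and the two periods isolate the sessions in which the arms differ. An on-treatment AE comparison is a legitimate choice, and the AE window need not match the HAMD-24 endpoint. This stands: the on-treatment test of the second hypothesis is not invalidated.

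A reader might infer that the whole safety comparison is cut short. The document does not support that. Examinations, laboratory tests, ECG and cognitive assessments count as safety data with no stated end. Manic symptoms and memory complaints have named instruments, which may pick up part of a late harm. A memory complaint that begins during the course and then persists is already an AE under the definition.

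A reader might also take the 3% to 7% as the share of harms captured. Acute effects probably cluster around sessions, so the share of events captured could be far higher. That less durable benefit under low charge would make Hybrid-ECT look safer is a possibility, not something the document shows.

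It can also be said that a journal article leaves AE reporting periods to the full protocol. That would answer silence. Here the article states a closed definition and two closed periods, which do not fit its own stated purpose for follow-up.

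**Conclusion.** The point holds in a limited form. As written, no discrete event that starts after the last session enters the comparison of AE numbers and severity, and this applies to the full 13 months or so of follow-up. The definition and the purpose given for follow-up need to be reconciled. The gap concerns delayed harms in the AE comparison only.

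This rests on reading treatment as the course of sessions, which the separate medication sections support, and on taking the two periods as exhaustive, as the text presents them. The number of events affected, and whether the omission would favour either arm, cannot be derived from the document. It is an inexpensive improvement, not a flaw that undermines the trial.

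**What to change.** In the AEs section, extend AE recording past the last session, using the follow-up visits already planned: all AEs to the one-month visit, and at least serious and psychiatric events (such as suicidal behaviour, manic switch and readmission) to the one-year visit. State that patients who stopped treatment early but remain in follow-up are included. Add a third analysis period, after the last session, beside the two existing ones, so that the planned on-treatment comparison is kept intact.

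If the sponsor prefers not to extend recording, the alternative is to say expressly that the AE comparison, and any conclusion of fewer side effects drawn from it, covers the treatment course only, and that chronic effects are judged from the follow-up assessments.

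The cost is an AE page at existing visits, an extra row in the AE tables, and somewhat more data collection and cleaning. Late events will be harder to attribute to the stimulus strategy because follow-up medication is individualised, so the third period should be reported separately and read with that in mind.
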